#### Unblinding and Verification Procedures

2.5.4

Unblinding protocol: Group allocation information was only revealed through the synchronized opening of all sealed copies of the allocation table, ensuring temporal alignment and procedural transparency.Allocation validation: Actual group assignments were systematically cross‐verified against the original randomization records through independent auditing, confirming compliance with the predetermined allocation scheme.

### Intervention

2.6

#### Control Group

2.6.1

Given that a considerable proportion of patients will require targeted treatment for underlying conditions such as hypertension, glycemic control, anticoagulation, and lipid regulation, concomitant therapies will be permitted during the study period. Moreover, each patient also underwent cognitive rehabilitation training five days a week with two days of rest for a total of 4 weeks. The standard drug treatment group was the control group. The enrolled patients will receive 5 mg of donepezil hydrochloride per night initially, which is increased to 10 mg per night after 30 days in the absence of any adverse reactions. The total treatment duration is 4 weeks.

#### Electroacupuncture Therapy

2.6.2

All participants who will be recruited for the study will have no previous exposure to psychotropic medication treatment. Treatment involved using sterile 0.25×50 mm stainless steel Hua Tuo brand filiform needles and the KWD‐808II universal pulse electrotherapy apparatus while patients were seated. The acupuncturist will needle the bilateral Fengchi (GB20) and Gongxue, located 1.5 cm below Fengchi (GB20) (General nomenclature of science of acupuncture and moxibustion 2013). Hands and the needling area will be disinfected with alcohol before needling. Needles will be inserted into the acupoints with a slight downward and toward the throat direction, reaching a depth of 20–25 mm. Electrotherapy will be applied to the Fengchi (GB20) and Gongxue (Figure 2B, Table 1) on the same side of the head, with sparse waves causing slight head movement (Liu et al. 2017). The current intensity will be adjusted to patient tolerance for 30 min per session. This procedure will be done once daily for four courses of treatment lasting one week each. To maintain treatment consistency, the same therapist will perform all acupuncture interventions for the patients.

**FIGURE 2 brb370631-fig-0002:**
[figure not shown]
The acupoints used in olfactory therapy and electronuchal acupuncture. **(A)** The points displayed on the face, green: Suliao (GV25); orange: Yingxiang (LI20); and **(B)** Acupoints shown behind the head, blue: Fengchi (GB20); red: Gongxue.

**TABLE 1 brb370631-tbl-0001:** Acupoints selected for use in the study.

Acupoints	Location	Manipulation
Fengchi (GB20) (bilateral)	On the nape, below the occipital, on a level with Fengfu (DU‐16), in the depression between the upper portion of the trapezius and the sternocleidomastoid	For normal manipulation, electric acupuncture will be used between the left Fengchi and Gongxue and the right Fengchi and Gongxue.
Gongxue (bilateral)	On the nape, located 1.5 inches straight down from Fengchi, level with the lower lip	For normal manipulation, electric acupuncture will be used between the left Fengchi and Gongxue and the right Fengchi and Gongxue.
Suliao (GV25)	On the human face, in the center of the tip of the nose.	Essential oil from ATR in a rollerball inhaler was applied uniformly to Suliao.
Yingxiang (LI20) (bilateral)	Open at the midpoint of the outer edge of the nose when it is in the nasolabial fold.	Essential oil from ATR in a rollerball inhaler applied uniformly to Yingxiang.

#### Herbal Olfactory Therapy

2.6.3

The baseline characteristics of the enrolled patients will be similar to those described in Section 2.5.2 (as above). Following enrollment, participants will receive an immediate traditional Chinese medicine olfactory diagnosis treatment conducted by a single therapist to eliminate potential biases. The therapy will involve using essential oil from ATR in a rollerball inhaler, applied uniformly to specific acupoints (Figure 2A, Table 1, Suliao (GV25), bilateral Yingxiang (LI20) (Zabor et al. 2020)) to enhance cognitive awakening. Participants will be instructed to inhale the oil for 5 to 10 min, three to five times daily, for 4 weeks while maintaining steady and regulated breathing.

#### Combination Group

2.6.4

The combination group will receive electroneutral acupuncture and olfactory therapy. The procedures were the same as in Sections 2.6.2 and 2.6.3.

#### The Healthy Group

2.6.5

Healthy participants will receive an immediate traditional Chinese medicine olfactory diagnosis treatment conducted by a single therapist to eliminate potential biases. The procedure is the same as in Section 2.6.1.

#### Sham Group

2.6.6

In the sham stimulation group, non‐penetrating acupuncture will make the patients experience a feeling similar to acupuncture. But it doesn't pierce the skin. Other treatments will be the same as Section 2.6.5.

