**Methods:**

This parallel‐group, assessor‐blinded, randomized controlled trial will recruit 210 PSCI patients, randomly assigned to one of six groups: control, EA, HOT, combination therapy, sham therapy, or the healthy (ratio 1:1:1:1:1:1). All participants will receive standard cognitive training and basic medical care. The EA group will receive 4 weeks of electro‐acupuncture at specific acupoints. The HOT group will receive 4 weeks of aromatic inhalation therapy using Acorus tatarinowii volatile oil. The combination group will receive both interventions. The primary outcome measure is cognitive function, assessed using the Montreal cognitive assessment (MoCA) at baseline, week 4, and week 8. Secondary outcomes include the mini‐mental state examination (MMSE), functional magnetic resonance imaging (fMRI), near‐infrared spectroscopy (fNIRS), and anxiety assessment using the state‐trait anxiety inventory (STAI) at baseline and week 4. Data analysis will be conducted using a modified intention‐to‐treat approach.

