In addition to the primary outcome measures, we also included some imaging examinations as secondary measures. fMRI is used to assess cerebral hemodynamics and identify activated brain regions to compare different groups (Logothetis 2008). fNIRS is a non‐invasive, portable, and cost‐effective method that measures changes in oxygenated and deoxygenated hemoglobin levels in the cerebral cortex using near‐infrared light, reflecting neural activity (Irani et al. 2007). fNIRS allows for convenient self‐control and observation of the brain during treatment, providing detailed insights into stimulated brain areas by acupuncture and Traditional Chinese medicine olfactory. Ultrasound Doppler is another non‐invasive method to examine cerebrovascular diseases by detecting hemodynamic and physiological changes in major intracranial arteries (Wan et al. 2022). These secondary measures help us understand participants' cerebral vascular function changes during treatment and offer preliminary evidence for further exploration of underlying mechanisms. Moreover, by comparing with the healthy population, this study more clearly revealed the abnormal brain function of patients with cognitive impairment after stroke and the effect of intervention on their brain function. This design not only enhances the scientific validity of the study results, but also provides a more reliable basis for clinical application.

The study design was limited to a single‐center study, resulting in a relatively small sample size. To enhance the robustness of the study, future studies should include more diverse cases from multiple centers. Additionally, the lack of a sham stimulation group as a control group due to controversies surrounding the need for sham acupuncture and its implementation is a limitation of this trial design. Subsequent experiments will delve into detailed basic research both in vitro and in vivo to uncover the molecular mechanisms behind HOT and EA treatment for enhancing cognitive function in stroke patients. While non‐pharmacological treatments show promise in addressing PSCI injuries, further extensive research and clinical trials are essential to validate their efficacy and safety. Therefore, the significance of this study lies in providing stronger evidence for the clinical application of these treatments.

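### The arm definitions contradict each other on donepezil, active oil and the sham arm, so what the control and sham contrasts test depends on how the text is read

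*Protocol article*

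**What the plan says.** All places are in the protocol article.

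- **Control, 2.6.1.** Donepezil is assigned here directly: "The standard drug treatment group was the control group". The next sentence has a wider subject: "The enrolled patients will receive 5 mg of donepezil hydrochloride per night initially". It stands under the control heading but does not say control patients only.
- **EA, HOT and combination, 2.6.2 to 2.6.4.** EA is described by its needling ("The acupuncturist will needle the bilateral Fengchi (GB20) and Gongxue"), HOT by oil inhalation, and the combination by reference to both sections. None of the three mentions donepezil as trial treatment. Section 2.6.2 excludes earlier psychotropic medication, which does not say what is given during the trial.
- **Background care, Abstract, Methods.** "All participants will receive standard cognitive training and basic medical care". No drug is named, and none is excluded.
- **Healthy group, 2.6.5.** "Healthy participants will receive an immediate traditional Chinese medicine olfactory diagnosis treatment", and then "The procedure is the same as in Section 2.6.1".
- **Sham arm, 2.6.6.** Non-penetrating needling, and then "Other treatments will be the same as Section 2.6.5".
- **Discussion.** A listed limitation is "the lack of a sham stimulation group as a control group due to controversies surrounding the need for sham acupuncture". The Abstract and sections 2.1, 2.4 and 2.6.6 all include a sham group.

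**The concern.** A contrast between two arms estimates the effect of whatever differs between them. If donepezil belongs to the control arm alone, EA versus control and HOT versus control compare a non-drug treatment with a drug. If every patient takes donepezil, the same contrasts estimate what EA or HOT adds. One MoCA difference would then support two different conclusions, and the article does not say which applies.

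The sham arm has the same problem. If it includes active oil, EA versus sham sets real needling against sham needling plus oil, and the oil may offset part of any EA effect. The healthy group is described in 2.4 as a reference for normal brain function, yet 2.6.5 gives it a treatment.

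The Abstract sets out to evaluate EA and HOT as single treatments as well as in combination, so these contrasts matter. An analysis plan cannot repair them, because the contents of the arms are what is in doubt.

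**Working it through.** No sample-size or power figure bears on this point. The check writes each arm as a set of components and takes differences.

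**Components.** EA = real electroacupuncture; S = sham needling; H = active oil; D = donepezil. Cognitive training is common to the patient arms and drops out.

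**Following the references.** 2.6.6 points to 2.6.5, which gives H. 2.6.5 points to 2.6.1, which gives D. With donepezil only where it is printed or cross-referenced:

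- control = D
- EA = EA
- HOT = H
- combination = EA + H
- healthy = H + D
- sham = S + H + D

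**Readings compared**

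1. Literal, as above.
2. As 1, but 2.6.5 meant 2.6.3: sham = S + H, healthy = H.
3. As 1, but 2.6.6 meant 2.6.1: sham = S + D.
4. Donepezil for all patients, 2.6.6 as printed: D in every patient arm, sham = S + H + D.
5. Donepezil for all patients, 2.6.6 meant 2.6.1: sham = S + D.

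In each cell, the left side is found only in the first arm and the right side only in the comparator. Bold marks a contrast that isolates EA (against nothing, or against sham needling) or H.

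| Contrast | 1 | 2 | 3 | 4 | 5 |
|---|---|---|---|---|---|
| EA vs control | EA / D | EA / D | EA / D | **EA / none** | **EA / none** |
| HOT vs control | H / D | H / D | H / D | **H / none** | **H / none** |
| Combination vs control | EA+H / D | EA+H / D | EA+H / D | EA+H / none | EA+H / none |
| EA vs sham | EA / S+H+D | EA / S+H | EA / S+D | EA / S+H | **EA / S** |
| HOT vs sham | none / S+D | none / S | H / S+D | none / S | H / S |
| Combination vs sham | EA / S+D | **EA / S** | EA+H / S+D | **EA / S** | EA+H / S |
| Contrasts isolating EA or H | 0 of 6 | 1 of 6 | 0 of 6 | 3 of 6 | 3 of 6 |

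Where HOT versus sham differs only in S (readings 2 and 4), it measures sham needling and says nothing about the oil.

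**Main aim.** Combination minus EA = H, and combination minus HOT = EA, in all five readings. This holds because 2.6.2 to 2.6.4 treat donepezil alike: none of them mentions it.

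**Healthy group.** It is H + D when 2.6.5 is read literally and H if 2.6.5 meant 2.6.3. It receives the olfactory treatment either way, because the first sentence of 2.6.5 says so.

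**The case against.** The strongest reply is that these are editing slips. The first sentence of 2.6.5 repeats the description of the olfactory treatment in 2.6.3, so its pointer may simply be wrong. Section 2.6.3 has another faulty pointer: it sends the reader to 2.5.2, the allocation table, for patient characteristics. This carries weight. A reader might infer that the trial plans donepezil for healthy volunteers. The documents do not support that as an intention; it is only what the printed reference yields. But correcting this one pointer (reading 2) still leaves oil in the sham arm and donepezil unresolved in the control contrasts.

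A second reply is that a drug comparator is a legitimate design and that 2.6.1 assigns donepezil to control without any cross-reference. Both are true. The ambiguity in the control contrasts comes from the unclear scope of the drug, not from misdirected references. The Abstract's description of EA and HOT as non-drug, single treatments suggests that donepezil is for control only, but it does not settle the matter.

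A third reply is that the healthy reference is not lost. This stands for baseline: Table 2 schedules fMRI at week 0, and section 2.4 neither calls the cohort untreated nor ties the reference to week 4.

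On the sham arm, four places include it and only the Discussion denies it. The contradiction remains, but it is one-sided.

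**Conclusion.** The arm definitions are inconsistent as written, and they decide what the control and sham contrasts can show. Of those six contrasts, none, one or three isolate EA or HOT, depending on the reading; on the literal reading none does. The evaluation of EA and HOT as single treatments is therefore not interpretable until the text is reconciled.

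A reader might go further and infer that no control or sham contrast can isolate either treatment. The documents do not support that. EA versus control and HOT versus control do so if all patients take donepezil. Combination versus sham isolates EA against sham needling if 2.6.6 stands as printed and either 2.6.5 meant 2.6.3 or all patients take donepezil. Nor is the main aim compromised: combination versus each monotherapy differs by one component throughout, provided the EA, HOT and combination arms are handled alike for donepezil.

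The conclusion rests on the text alone. The direction of any bias cannot be stated without knowing which reading the site follows.

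**What to change.** 1. Reconcile the Abstract (Methods), sections 2.4 and 2.6.1 to 2.6.6, and the Discussion.
2. Correct the cross-references in 2.6.5 and 2.6.6, and state in 2.6.1 which arms donepezil applies to.
3. Add one table with a row for each of the six groups and yes/no columns for donepezil, cognitive training, active oil, real EA and sham needling.
4. Bring the Discussion's statement on the sham group into line with the design sections.
5. Claim a specific effect of EA or HOT only from contrasts that, by that table, differ in that one component.

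Which treatments each arm receives is for the investigators to decide; this point proposes none. The cost is wording, two corrected references and one table, plus notification of the ethics board if site practice has differed from the approved text. Sample size, schedule and data collection do not change.

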### Clinical Assessment

2.7

#### Primary Outcomes

2.7.1

Participants' cognitive abilities will be assessed at three‐time points: baseline (week 0), during treatment (week 4), and follow‐up (week 8) (Table 2). The primary outcome measures include the Montreal Cognitive Assessment (MoCA), which are commonly used tools for evaluating cognitive function across different types of impairment.

**TABLE 2 brb370631-tbl-0002:** Schedule of enrollment, intervention, and assessment.

	Week 0 (baseline)	Week 4	Week 8
MMSE	X	X	X
MoCA	X	X	X
MBI	X	X	X
TCD	X	X	
fNIRS	X	X	
fMRI	X	X	
STAI	X	X	
Adverse Effects			

#### Secondary Outcomes

2.7.2

The mini‐mental state examination (MMSE): MMSE score will be assessed at three‐time points: baseline (week 0), during treatment (week 4), and follow‐up (week 8).The Modified Barthel Index (MBI): MBI scores will be utilized to evaluate patients' activities of daily living and their level of dependency. It will be assessed at three‐time points: baseline (week 0), during treatment (week 4), and follow‐up (week 8).Transcranial Doppler (TCD)

TCD involves the following steps: First, prepare the equipment, including the transcranial Doppler ultrasound device and the probe, ensuring that the device is properly calibrated and the appropriate parameters are set. Second, prepare the patient or subject, who is typically placed in a supine or sitting position, with ultrasound coupling gel applied to the scalp to ensure sound wave conduction, and the detection points are marked. Finally, detect the cerebral vessels by selecting the appropriate detection window (such as the temporal window, occipital window, and ophthalmic artery window), and adjust the probe angle and position to locate the target cerebral vessels.

Parameter settings: The light source wavelength typically employed ranges from near‐infrared light of 650 to 900 nm, as this range exhibits low absorption of light by both hemoglobin and water. The light source can be either a pulsed laser or an ultra‐short pulsed laser. Detection is performed using a Time‐Correlated Single Photon Counting (TCSPC) detector, which allows for time resolution at the picosecond (ps) level to measure the time of flight of photons. The probe layout generally maintains a distance of 2 to 4 cm between the light source and the detector.

Analysis method: Temporal point spread function (TPSF): This method involves analyzing the time‐of‐flight distribution of photons to derive the optical characteristics of tissue, specifically the absorption coefficient and scattering coefficient. Differential Pathlength Factor (DPF): This factor is employed to correct the path length of photons traveling through tissue. Calculation of Hemoglobin Concentration: The concentration changes of oxygenated hemoglobin (HbO2) and deoxygenated hemoglobin (HbR) are calculated based on variations in the absorption spectrum.
4Near‐infrared spectroscopy (fNIRS)

fNIRS is a non‐invasive neuroimaging technique that evaluates regional blood oxygen metabolism in the brain by emitting near‐infrared light and detecting its scattered signals within brain tissue. When using fNIRS, the first step is to prepare the equipment, including near‐infrared light sources and detectors, and ensure proper device calibration. Participants are typically positioned in a comfortable seated or supine position, with their scalp cleaned to minimize light wave interference. The light sources and detectors are then secured at specific brain regions (e.g., the frontal or parietal lobes) using headbands or fixation devices to maintain stability. During data acquisition, the device records changes in the concentrations of oxygenated hemoglobin (oxy‐Hb) and deoxygenated hemoglobin (deoxy‐Hb) in brain tissue, reflecting hemodynamic dynamics associated with brain activity.

Light source wavelength: Typically, two or more wavelengths, such as 750 nm and 850 nm, are employed to differentiate between oxyhemoglobin (HbO2) and deoxyhemoglobin (HbR). Light source type: Continuous wave lasers or LEDs are commonly utilized. Sampling rate: A frequency range of 10–50 Hz is generally adopted to effectively capture the dynamic changes in blood oxygen levels. Probe layout: The distance between the light source and the detector is maintained at 2–3 cm to ensure accurate detection of cerebral cortex activity. Number of channels: Depending on experimental requirements, the system may incorporate 16 channels, 32 channels, or more.

The analysis method involves a revised application of Beer‐Lambert's law, which is utilized to convert variations in light intensity into corresponding changes in hemoglobin concentration. Baseline correction is employed to eliminate low‐frequency drift and high‐frequency noise from the signal. Task‐related signal extraction involves the extraction of blood oxygen signals associated with specific tasks, utilizing either the general linear model (GLM) or an event‐related averaging method, akin to ERP analysis. Finally, functional connectivity analysis is conducted to calculate the functional connections between different brain regions, employing metrics such as the Pearson correlation coefficient or phase synchronization.
5Functional magnetic resonance imaging (fMRI)

fMRI is a high spatial resolution neuroimaging technique that maps brain functional activity by detecting blood‐oxygen level‐dependent (BOLD) signals.

Parameter settings for the imaging process include a magnetic field strength typically set at 3 Tesla (T), although devices with field strengths of 7T or higher are also available. The scan sequence utilizes a gradient echo planar imaging (EPI) sequence to capture blood‐oxygen‐level‐dependent (BOLD) signals. The time resolution (TR) is 3 s. The spatial resolution is typically 2 mm isotropic voxel. Scanning is conducted in a manner that encompasses the entire cerebral cortex through whole‐brain scans.

The analysis method involves several preprocessing steps: Realignment to remove head motion artifacts, normalization to map the individual brain to a standard space (such as MNI space), and smoothing using a Gaussian kernel to enhance the signal‐to‐noise ratio. For resting state analysis, functional connectivity is assessed by calculating time series correlations between different brain regions. Additionally, Independent Component Analysis (ICA) is employed to extract resting state networks, such as the default mode network.
6The state‐trait anxiety inventory (STAI)

State‐Trait Anxiety Inventory is a self‐report assessment of state anxiety and trait anxiety, including two subscales, State‐Trait Anxiety Inventory‐State (STAI‐S) and State‐Trait Anxiety Inventory‐Trait (STAI‐T). STAI‐S and STAI‐T are used for assessment the temporary condition of state anxiety and the more general and long‐standing quality of trait anxiety, respectively. Each subscale consists of 20 items. The STAI‐S scale is rated on 4‐point likert scale (1 = not at all, 2 = somewhat, 3 = moderately and 4 = very much). Each STAI‐T item is rated on a 4‐point Likert scale as well (1 = rarely, 2 = sometimes, 3 = often and 4 = almost always). STAI has been shown to have good internal consistency and test‐retest reliability.

### Data Security and Monitoring

2.8

The data management of this study is overseen by the research team to uphold the authenticity, integrity, confidentiality, and traceability of clinical trial data. The Case Report Form (CRF) will be completed by the principal investigator or other authorized researchers, with only qualified medical researchers permitted to input raw clinical assessment/safety data. Any modifications made to the raw data on the CRF by the principal investigator or other authorized researchers will be recorded. Approved data modifications necessitate the researcher making the changes by signing their name, indicating the modification date, and providing the rationale for the modification. Researchers will adhere to standard operating procedures to ensure quality control of the clinical trial and the implementation of a quality assurance system. All observed results and findings in the clinical trial will be validated to guarantee the data's reliability and to ensure that all conclusions drawn from the clinical trial are based on original data. Quality control measures will be enforced throughout the data processing stages to verify the reliability and accuracy of all processed data.

